### Participant timeline {13}

Table 1 shows the timeline of participant assessments/interventions.

**Table 1 Tab1:** Study timeline of participant assessments/interventions

Process	Screening/baseline/randomization	Treatment phase	Follow-up phase		
	B/L/D0	D1–D10	D14 ±1	D21 ±3	D28 ±3
Inclusion/exclusion criteria	X				
Written informed consent	X				
Demographics	X				
Assessment of concomitant chronic diseases	X				
Efficacy/safety assessment					
ECG	X		X		
Chest imaging	X	X (only on D10)			X
Vital signs (body temperature, heart rate, blood pressure, breathing rate, oxygen saturation, etc.)	X	X	X	X	X
Clinical symptoms assessment (fever, cough, diarrhea, dyspnea)	X	X	X	X	X
Primary endpoint assessment	X	X	X	X	X
Adverse events	X	X	X	X	X
**Laboratory test**					
Diagnosis (clinical diagnosis, antibody diagnosis, or pathogen diagnosis)	X				
Whole blood count (sampling time)	X	X (only on D3, D7, and D10)			
Coagulation routine (sampling time)	X	X (only on D3, D7, and D10)			
Kidney and liver function tests (sampling time)	X	X (only on D3, D7, and D10)			
Arterial blood gas analysis	X				
Pregnancy test (urine/blood, for women of childbearing age only)	X				
Nasopharyngeal/ oropharyngeal swab	X	X	X	X	X
Lower respiratory tract specimen (sputum/tracheal aspirate/bronchial alveolar lavage fluid) if available	X	X	X	X	X
Feces/anal swabs	X	X	X	X	X
Pharmacokinetic sampling (approximately 4 ml whole blood)		X (only on D1, D3, D7 [as needed], and D10)			
**Interventions**					
Remdesivir/placebo		X			
Concomitant medications (record only)	X	X	X	X	X

### Sample size {14}

The primary outcome is TTCI (censored at day 28). An interim analysis for futility and efficacy is planned at the midpoint of the trial. At this point the sample size may also be re-assessed. A one-sided type I error of 2.5% across the two stages of the trial and a power of 80% if the hazard ratio comparing remdesivir to placebo is 1.4 is used. This hazard ratio corresponds to a reduction in TTCI to 15 days on remdesivir if the TTCI on standard of care was 21 days. Triangular boundaries [16] are used to account for the multiple looks at the data, and allowance for the 2:1 randomization in favour of remdesivir is made. Under these assumptions, the total number of events required in this study is 325.

Assuming an 80% event rate within 28 days across both arms and a dropout rate of 10% implies that approximately 453 patients are to be recruited for this trial (151 on placebo and 302 on remdesivir).

### Recruitment {15}

Patients will be recruited from the designated hospitals for patients with COVID-19 virus.

### Assignment of interventions: allocation

#### Sequence generation {16a}

A permuted block (30 patients per block) randomization sequence, including stratification, is prepared by a statistician not involved in the trial using SAS software, version 9.4 (SAS Institute). Patient randomization is stratified based on respiratory support methods at the time of enrolment: (1) no oxygen support, oxygen support with nasal duct or mask; (2) high-flow oxygen, NIV, IMV/ECMO.

#### Concealment mechanism {16b}

Eligible patients were allocated to receive medication in individually numbered packs according to the sequential order provided by the randomization centre (Jin Yin-tan Hospital central pharmacy). Remdesivir and placebo are pre-blinded and stored in a secure area in the pharmacy at a temperature strictly controlled according to the protocol. An independent pharmacist is assigned to dispense the study drug in waterproof, sealed, opaque bags.

#### Implementation {16c}

Patients will receive medication in individually numbered packs according to the sequential order provided by the randomization centre. Opaque envelopes were provided for emergency unblinding events. The allocation sequence was generated by the institutes of Materia Medica, Chinese Academy of Medical Sciences & Peking Union Medical College. Participants are enrolled by the investigators of each study site. A pharmacist in the central pharmacy assigns participants to interventions.

### Assignment of interventions: blinding

#### Who will be blinded? {17a}

This is a double-blind trial. Trial participants, investigators, care providers, outcome assessors, and data analysts are all blinded. Treatment allocation will only be unblinded after database lock.

### Procedure for unblinding if needed {17b}

Unblinding is permissible when investigators believe that there is a very strong need to know the study drug allocation in order to perform any agent treatment/action. Whenever possible, unblinding will only be conducted after discussion with the study principal investigator. The procedure for revealing a participant’s allocated intervention is as follows: (1) investigators confirm that the patient meets the criteria of unblinding according to the protocol; (2) the independent pharmacist opens the sealed envelope and informs the investigators of the allocation; (3) information about the date, time, and reason of unblinding will be recorded in the electronic data capture (EDC) system and the envelope; (4) the envelope must be sealed again as soon as possible and securely stored along with the primary files of the subject.

### Data collection and management

#### Plans for assessment and collection of outcomes {18a}

Investigators are responsible for assessment and collection of outcome, baseline, and other trial data, and the data are double checked by the clinical research coordinators and clinical research associates as well as data managers. Nasopharyngeal/oropharyngeal swabs, lower respiratory tract specimens (sputum/tracheal aspirate/bronchial alveolar lavage fluid), feces/anal swabs, and pharmacokinetic samples (whole blood) will be sent to a central laboratory, where tests will performed according to laboratory standard operating procedures (SOPs). Data collection forms can be found at https://edc.clinflash.net/login.

For the efficacy outcome measures, two scales (six-category ordinal scale of clinical status and NEWS2) are used. Investigators will be trained to use these scales.

#### Plans to promote participant retention and complete follow-up {18b}

Subjects may voluntarily withdraw from the trial at any time. This decision must be communicated with and reviewed by investigators. Staff at study sites should explain to these subjects the importance of staying in the study for the full duration of follow-up of this trial. For any withdrawal from this trial, investigators must fill in the withdrawal reason in the electronic case report form (eCRF) and try to complete all remaining assessments up to day 28 after randomization. For subjects who withdraw due to AEs, investigators should closely follow up their AEs until the AEs disappear, return to the baseline state, or the AE condition is stable. If subjects are lost to follow-up, existing data collected up until the time of loss to follow-up will be used.

Investigators may request for subjects to be withdrawn from receiving the study drugs for clinical or other reasons. In this case, subjects should remain in the trial after terminating the trial treatment and be followed up for all scheduled visits and the corresponding data recorded.

#### Data management {19}

The EDC system will be used for data management, including data entry, query, coding, security, and storage. The data manager built the database according to the protocol, and at the same time made logical verification settings for data validity, so as to verify the data. The data of each enrolled subject (including discontinued subjects) will be recorded into the database/eCRF rapidly, completely, and accurately. Each completed eCRF will be reviewed and signed (electronically) by the investigators. The data manager will check the data and ask investigators to resolve any queries identified. The data administrator will proofread and modify the data according to investigators’ answers. The data are securely stored in the EDC system, with the server located in Zhejiang Province, China.

### Confidentiality {27}

Subjects’ data collected in CRFs will be identified by a study subject ID only. Samples collected through the study will also be identified by a study subject ID only. The log linking the study subject ID with the patient identifying information will be held at each recruitment site. In the emergent or rare event that, for safety or regulatory reasons, it may be necessary to identify a subject, the sponsor and investigators were bound to keep this information confidential.

### Plans for collection, laboratory evaluation, and storage of biological specimens for genetic or molecular analysis in this trial/future use {33}

Nasopharyngeal/oropharyngeal swabs, lower respiratory tract specimens (sputum/tracheal aspirate/bronchial alveolar lavage fluid), feces/anal swabs, and pharmacokinetic samples (whole blood) will collected by investigators or designees, marked with the study subject ID, and then immediately sent to the central laboratory for coronavirus nucleic acid detection or remdesivir/active metabolites concentration detection. Sample collection, handling, labelling, storage, shipping, processing, etc. will be performed according to the requirements of the operation manual in the central laboratory, Teddy Clinical Research Laboratory (Shanghai) Ltd.

### Statistical methods

#### Statistical methods for primary and secondary outcomes {20a}

The primary outcome is TTCI up to day 28 of patients on remdesivir compared to patients receiving placebo. Patients will be randomized at a ratio of 2:1 to receive either remdesivir or placebo. All reporting will adhere to the Consolidated Standards of Reporting Trials (CONSORT) guideline as well as the corresponding extension for adaptive clinical trials [17, 18].

The final analysis of the primary endpoint will use a Cox proportional hazards model following the intention-to-treat principle. The final analysis will be conducted once a total of 325 events have occurred across both treatment groups. Under the assumption of an 80% event rate within 28 days and accounting for 10% dropout, this means that the maximum number of patients to be recruited is approximately 453. A standardized test statistic is then found on the basis of this model—if this test statistic exceeds 2.095, then it will be concluded that remdesivir is significantly better than placebo. Median unbiased effect estimates and confidence intervals accounting for the interim analysis will be reported [19]. Analysis of secondary endpoints will use a logistic model for binary variables such as mortality and a Cox proportional hazards model for time-to-event endpoints. A statistical analysis plan (SAP) providing all details of the analyses to be undertaken will be completed before any data analysis will be conducted.

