### 3.18.2. Interim analyses {21b}

An interim analysis for efficacy and lack of benefit will be undertaken once a total of 163 events have been observed across all treatment group. For the interim analysis the primary endpoint will be analysed using a Cox proportional hazards model using the intention-to-treat principle. A standardized test statistic is then found on the basis of this model and if this test statistic falls below 0.741, the trial will be stopped for lack of benefit of remdesivir. If the test statistic exceeds 2.222, the trial will terminate with the conclusion, that remdesivir is significantly better than control. If the test statistics falls between 0.741 and 2.222, the trial continues to the second stage and a sample size re-estimation on the basis of the observed event rate will take place. The interim analysis is to be conducted by an independent statistician and reviewed by the DSMC. Should the trial stop for futility or efficacy the median unbiased estimate as well as confidence intervals accounting for the interim analysis will be reported [19].

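### The interim and final Cox models are described without the respiratory-support stratum used in randomisation; stratifying them is a free gain in power whose size depends on unstated prognostic strength

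*Protocol article*

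**What the plan says.** Sequence generation {16a} of the protocol article states: "Patient randomization is stratified based on respiratory support methods at the time of enrolment". There are two levels. One covers no oxygen, or oxygen by nasal duct or mask. The other covers high-flow oxygen, non-invasive ventilation, and invasive ventilation or ECMO.

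Statistical methods for primary and secondary outcomes {20a} gives the final test: "The final analysis of the primary endpoint will use a Cox proportional hazards model following the intention-to-treat principle". Its standardised statistic is compared with 2.095. Interim analyses {21b} gives the interim test: "For the interim analysis the primary endpoint will be analysed using a Cox proportional hazards model using the intention-to-treat principle". Its statistic is compared with 0.741 (lack of benefit) and 2.222 (efficacy). Neither section includes or excludes the stratum. The additional analyses in {20b} name only gender and age. Section {20a} also says that a statistical analysis plan with all analysis details will be completed before any data analysis; that plan is not at hand.

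Sample size {14} assumes "a power of 80% if the hazard ratio comparing remdesivir to placebo is 1.4 is used", explained as "a reduction in TTCI to 15 days on remdesivir if the TTCI on standard of care was 21 days", and concludes that "the total number of events required in this study is 325".

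**The concern.** The article fixes the decision rule to three decimals but describes the model behind each Z statistic without the one factor that structured the randomisation.

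A Cox model with a single baseline hazard across groups that improve at different rates estimates a treatment hazard ratio closer to 1 than the ratio within groups. It also makes no use of the balance that stratified allocation creates. If the drug works, Z tends to be smaller than it need be. The trial is then somewhat more likely to fall below 0.741 at the interim look and somewhat less likely to pass 2.222 or 2.095.

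The endpoint definition gives a reason, from the article alone, to doubt one shared baseline hazard. A patient in category 3 needs a fall of two categories, which is discharge, and a patient in category 2 can qualify only by discharge. A patient in category 4 or 5 can qualify in hospital (4 to 2, 5 to 3). The strata therefore reach the endpoint by different transitions. This does not show which stratum improves faster or by how much.

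**Working it through.** **1. Inputs from the protocol article.** One-sided type I error 0.025 over two stages; 80% power at HR 1.4; 2:1 allocation; looks at 163 and 325 events; bounds 0.741/2.222 and 2.095; 80% event rate by day 28; 10% dropout; about 453 patients.

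**2. The plan's own figures.**
- Planning effect: 21/15 = 1.4.
- Bounds: the triangular form with C = 2.095/2 = 1.0475 gives 1.5C/√0.5 = 2.222, 2C = 2.095 and 0.5C/√0.5 = 0.741. Numerical integration gives a one-sided error of 0.0250, as stated.
- Events: the fixed-sample Schoenfeld formula gives (1.960 + 0.842)² / [(2/9)(ln 1.4)²] = 312. The two-stage inflation factor is 1.132, giving 353 events, or 76.6% power at 325. The Freedman formula (2:1, ratio taken as 1/1.4) gives 283.5 × 1.132 = 321, within 3% of 325. The stated figure is therefore reproduced, but only under some variants of the formula.
- Patients: 325/0.8 = 406.25, and 406.25/0.9 = 451.4, so 452 against the stated 453.

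**3. Effect of leaving the stratum out.** The article gives neither the share of patients in the high-support stratum nor its effect on improvement, so both are assumptions and are varied. Setting: exponential times censored at day 28, 2:1 allocation within strata, 407 analysed patients, an 80% overall event rate (about 325 events), HR 1.4 within each stratum, the protocol's bounds, 12,000 simulated trials per cell. The stratified test has about 75% power in every cell, in line with the 76.6% above. Loss of power from the unstratified test, in percentage points:

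| Between-stratum HR (high vs low support) | share 10% | 18% | 30% | 50% |
|---|---|---|---|---|
| 0.7 | 0 | 1 | 1 | 1 |
| 0.5 | 1 | 3 | 4 | 5 |
| 0.4 | 2 | 5 | 7 | 10 |
| 0.3 | 3 | 9 | 12 | 18 |
| 0.2 | 5 | 15 | 23 | 31 |

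At a 30% share, power is 71.4% unstratified against 75.0% stratified for a between-stratum HR of 0.5, and 62.4% against 74.6% for 0.3. The estimated treatment HR is about 1.36 and 1.31 unstratified, against about 1.38 stratified. These are one-step score estimates, so even the stratified value sits slightly below 1.40.

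A separate simulation with 325 events and shares of 20-50% gives losses of about 0-2 points at 0.7, 2-5 at 0.5, 3-10 at 0.4 and 6-18 at 0.3. Futility stops rise by about 0-8 points.

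**4. Sensitivity to the event rate.** Exponential medians of 21 and 15 days imply 28-day event rates of 1 − 2^(−28/21) = 0.603 and 1 − 2^(−28/15) = 0.726. Weighted 1:2, this is 0.603/3 + 2 × 0.726/3 = 0.685. At that rate and a 30% share, the losses are about 3, 6 and 9 points for between-stratum HRs of 0.5, 0.4 and 0.3.

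**5. Under no effect.** At a 30% share and a critical value of 1.96, the unstratified test has a one-sided error of about 0.020 (between-stratum HR 0.5) and 0.013 (0.3). The stratified test gives 0.024 and 0.021. The unstratified test is conservative, not invalid.

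**The case against.** The strongest reply is that silence is not exclusion. The article names a Cox model and defers details to an analysis plan that is not shown, and strata or covariates are commonly specified there. This stands: a reader might infer that the trial ignores its stratification factor, and the article does not establish that. It does not dispose of the point, because the article did not leave the primary test wholly to the later plan. It names the model and ties numerical stopping bounds to it, and someone following that text would fit an unstratified model.

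A reader might also infer that power falls by 10 points or more. The documents do not support that as a general figure. It needs a between-stratum HR of about 0.4 with half the patients in the high-support stratum, 0.3-0.35 at a 30% share, or about 0.25 at 18%. The endpoint also gives some reason to doubt a large contrast, since high-support patients can count as improved without leaving hospital. Nothing in the article ranks respiratory support as the strongest predictor of improvement.

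Finally, Sample size {14} ties HR 1.4 to improvement times of 15 and 21 days and does not say whether it applies within strata or overall. If 1.4 is the overall ratio, the unstratified test targets the planned effect and loses nothing against plan. Stratifying is then an efficiency gain forgone, not a flaw in the sample size. It would be wrong to say that the plan assumes a homogeneous population.

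**Conclusion.** The point holds as a conditional efficiency gain, with moderate confidence. Randomisation is stratified, and the models that produce the interim and final Z statistics are described without the stratum. Run that way, the test is valid but conservative, and the hazard ratio is attenuated if the strata differ in improvement rate. The direction is secure. The size rests on assumed stratum shares of 20-50%, an assumed between-stratum hazard ratio and a within-stratum treatment HR of 1.4. It runs from nothing noticeable with a weak stratum effect to 6-18 points of power with a strong one (0.3); a moderate effect (0.5) costs 2-5 points. It is not a demonstrated error in the design.

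**What to change.** In {20a} and {21b}, state that the primary Cox model is stratified by the randomisation stratum, with a separate baseline hazard for each level, and that its treatment Z statistic is the one compared with 0.741, 2.222 and 2.095. Carry the same wording into the statistical analysis plan before any interim look. If the plan already says this, only the article's wording needs aligning.

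The cost is one phrase in each place. The stratum is known for every patient at randomisation, so no new data are needed, and the bounds and event targets can stay as they are.

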### 3.18.2. Interim analyses {21b}

An interim analysis for efficacy and lack of benefit will be undertaken once a total of 163 events have been observed across all treatment group. For the interim analysis the primary endpoint will be analysed using a Cox proportional hazards model using the intention-to-treat principle. A standardized test statistic is then found on the basis of this model and if this test statistic falls below 0.741, the trial will be stopped for lack of benefit of remdesivir. If the test statistic exceeds 2.222, the trial will terminate with the conclusion, that remdesivir is significantly better than control. If the test statistics falls between 0.741 and 2.222, the trial continues to the second stage and a sample size re-estimation on the basis of the observed event rate will take place. The interim analysis is to be conducted by an independent statistician and reviewed by the DSMC. Should the trial stop for futility or efficacy the median unbiased estimate as well as confidence intervals accounting for the interim analysis will be reported [19].

### 3.18.3. Methods for additional analyses (e.g. subgroup analyses) {20b}

Separate supporting analysis will be undertaken for gender and age groups (<60 and over 60 years of age at randomization). These analyses will use a Cox proportional hazards model of the primary endpoint. Additionally, mortality will be analysed for each of these subgroups using a logistic regression model.

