## Introduction

### Background and rationale {6a}

In December 2019, Wuhan City, Hubei Province experienced an outbreak of pneumonia of unknown cause. On 7^th^ January 2020, a previously unidentified betacoronavirus, later named SARS-CoV-2 virus (or the disease named COVID-19), was identified by the Chinese Center for Disease Control and Prevention (China CDC) as the aetiological agent [1]. The SARS-CoV-2 probably derived originally from bats, and amongst coronaviruses known to infect humans, is most closely related to, but distinct from, the SARS coronavirus. The clinical manifestations of COVID-19 virus infection include asymptomatic infection, mild upper respiratory symptoms, severe viral pneumonia with respiratory failure, and even death. Although the risk of severe illness is not yet clear, hospitals in areas with significant community transmission have experienced a major increase in the number of hospitalized pneumonia patients, with the frequency of severe disease in hospitalized patients being as high as 30% [2–4]. The progression from prodromes (usually fever, fatigue, and cough) to severe pneumonia requiring oxygen support, mechanical ventilation, or extracorporeal membrane oxygenation (ECMO) is most commonly seen in the second week following onset of symptoms of a viral infection [2]. The kinetics of viral replication in the respiratory tract has not been well characterized, but this relatively slow progression provides a potential time window and opportunity for antiviral therapies to influence the course of the disease.

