#### Secondary outcome measures:The secondary outcome measures are the following:

Percentage of subjects in each clinical category on the six-category ordinal scale (time frame: days 7, 14, 21, and 28)Time to disease improvement, defined as the time to hospital discharge, or NEWS2 (National Early Warning Score 2) of ≤ 2 maintained for 24 h (time frame: up to 28 days)All-cause mortality (time frame: up to 28 days)Duration (days) of IMV (time frame: up to 28 days)Duration (days) of supplemental oxygenation (time frame: up to 28 days)Length of hospital stay (days) (time frame: up to 28 days)Incidence of nosocomial secondary infectionTime to SARS-CoV-2 virus RT-PCR negativity in upper and lower respiratory tract specimens (time frame: up to 28 days)Change (reduction) in SARS-CoV02 viral RNA load in upper and lower respiratory tract specimens as assessed by area under viral load curve (time frame: up to 28 days)Pharmacokinetic parameters of remdesivir or its active metabolitesFrequency of SAEs (time frame: up to 28 days).

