## Discussion

This study is the first double-blind, placebo-controlled trial of an experimental therapeutic for COVID-19. Whilst the COVID-19 epidemic has been declared a public health emergency of international concern, this does not negate the need to generate robust evidence in which healthcare professionals, patients, their families, and public health authorities can have confidence. In past epidemics, unproven treatments have been used on a compassionate use basis, in observational studies, or in underpowered trials, and the results are uncertainty and ongoing treatment dilemmas. Randomized, placebo-controlled trials are well established as the best way to minimize bias and confounding and produce reliable evidence. Such trials can be implemented even in the most difficult circumstances; in fact, the difficult circumstances themselves make it even more important that patient care is not driven by fear and rumour but by science and evidence. During health emergencies, doctors and politicians are under enormous pressure to find cures to save lives and stop the epidemic, whilst patients are willing to try anything in the face of a frightening and unknown threat. We must resist these pressures and make sure that patients benefit from the fruits of science, even in difficult times.

The use of placebo is especially beneficial in the midst of great anxiety, when the pressures to announce a cure or act on preliminary, but inconclusive data, are intense. A placebo relieves the temptation from all involved in the trial to engage in speculation and the worry that they are withholding what early (but often false) impressions may suggest is a promising drug. Whilst remdesivir has shown promising activity in preclinical models of severe CoV infection, it is currently unknown whether it will prove safe and effective in treating severe COVID-19, both because of its uncertain antiviral efficacy and the unclear importance of ongoing viral replication versus an inflammatory process in disease pathogenesis in severely ill patients. Of note, remdesivir yielded positive results in preclinical models of Ebola virus infection but was inferior to two monoclonal antibody therapies in treated patients [15].

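### The supporting analyses cover gender and age only; none asks whether clinical effect depends on time from symptom onset, the factor the rationale points to

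*Protocol article*

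**What the plan says.** - **Supporting analyses** (section 3.18.3, item 20b): "Separate supporting analysis will be undertaken for gender and age groups", with age divided at 60 years. TTCI is analysed in these groups with a Cox model and mortality with a logistic model. No other factor is named.
- **Rationale** (Background and rationale, item 6a): progression to severe pneumonia "is most commonly seen in the second week following onset of symptoms of a viral infection", and "this relatively slow progression provides a potential time window and opportunity for antiviral therapies to influence the course of the disease".
- **Acknowledged uncertainty** (Discussion): the article refers to "the unclear importance of ongoing viral replication versus an inflammatory process in disease pathogenesis in severely ill patients".
- **Entry** (Eligibility criteria, item 10): at most 12 days since symptom onset.
- **Stratification** (Sequence generation, item 16a): "Patient randomization is stratified based on respiratory support methods at the time of enrolment", in two levels. Onset time is not a factor.
- **Primary model** (items 20a and 21b): a Cox model at the interim and final analyses, with no covariates named.
- **Virology** (Secondary outcome measures, item 12): time to "virus RT-PCR negativity in upper and lower respiratory tract specimens", and reduction in "viral RNA load in upper and lower respiratory tract specimens as assessed by area under viral load curve", both to day 28.
- **Analysis plan** (item 20a): a SAP with the analysis details is to be completed before any data analysis. It is not shown.

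**The concern.** The article does not leave subgroup analysis entirely to the SAP: it names factors, endpoints and models. It gives no reason to expect the effect to vary by gender or age. The one dimension along which its background suggests that an antiviral might matter more or less, position in the disease course, is absent from the list.

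If the clinical effect does weaken with time from onset, the pooled hazard ratio is an average over patients who respond and patients who respond less. A disappointing pooled result would then invite the question of whether patients treated sooner after onset benefited, and the protocol states no analysis that addresses it. The interim rule sharpens this, because a standardized statistic below 0.741 at 163 events stops the trial for lack of benefit. Onset time is also left to chance between the arms, with 151 patients planned on placebo.

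**Working it through.** **Inputs from the article.** One-sided type I error 2.5%; 80% power at hazard ratio (HR) 1.4; 2:1 allocation; looks at 163 and 325 events; interim bounds 0.741 (lack of benefit) and 2.222 (efficacy); final bound 2.095.

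**Assumed, because the documents do not say.** HR 1.4 in early patients and 1.0 in late patients; late share of events 0.25, 0.33 or 0.50.

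**Step 1: the stated design.** Information = events × (1/3)(2/3) = events × 2/9. The mean of the test statistic is ln(HR) × √information, and the correlation between looks is √(163/325).
- HR 1.0: probability of crossing an efficacy bound is 0.02499, which reproduces the stated 2.5%.
- HR 1.4: the means are 0.3365 × √36.22 = 2.03 and 0.3365 × √72.22 = 2.86. Power is 76.6%, and the chance of an interim stop for lack of benefit is 10%.

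The gap between 76.6% and the stated 80% is a separate matter. Here 76.6% serves only as the undiluted reference.

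**Step 2: dilution.** Average HR = 1.4^(1 − late share), put through the same boundaries.

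| Late share of events | Average HR | Power | Interim stop for lack of benefit |
|---|---|---|---|
| 0 | 1.40 | 76.6% | 10% |
| 0.25 | 1.29 | 52% | 22% |
| 0.33 | 1.25 | 43% | 27% |
| 0.50 | 1.18 | 26% | 39% |

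**Step 3: what an onset-time analysis could show.** Take 325 events split half and half, so 162.5 per group. The variance of ln(HR) in each group is 4.5/162.5.
- SE of the difference in ln(HR) = √(2 × 4.5/162.5) = 0.235.
- For HR 1.4 versus 1.0: z = 0.3365/0.235 = 1.43. Power at two-sided 5% is Φ(1.43 − 1.96) ≈ 30%. With a 25/75 split it is about 24%.
- Ratio of hazard ratios detectable with 80% power, half/half: exp(2.80 × 0.235) ≈ 1.9.

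Stronger contrasts look better: 55% for HR 1.8 versus 1.1 and 84% for 2.0 versus 1.0. With an even split, however, these average to √(1.8 × 1.1) = √(2.0 × 1.0) = 1.41, to two decimals. They involve no dilution below the design HR and cannot be paired with the power losses in step 2.

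**The case against.** **The SAP may supply it.** The article condenses a protocol, promises a SAP before any data analysis, and does not call its subgroup list exclusive. Covariates and further subgroups are commonly set there. This stands to a large extent. It cannot be said that any look by onset time would be post hoc, or that a chance imbalance would go uncorrected. What remains is that the list the article does state omits the factor its rationale points to.

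**The 12-day limit does not contradict the rationale.** This stands. A reader might infer an early-treatment window that later entrants have missed. The background does not call the window early and gives it no end; it ties the window to slow progression into the second week, and day 12 falls within that week. The Discussion's doubt concerns severely ill patients rather than days from onset, and respiratory support, a marker of severity, is stratified.

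**An inactive drug could still be recognised.** A reader might infer that a diluted result could not be told apart from lack of antiviral activity, or that the viral samples go unused. The documents do not support either: time to RT-PCR negativity and the viral-load area under the curve are secondary outcomes that bear directly on activity. They do not show whether clinical effect varies with onset time.

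**The added analysis is weak.** This also stands: about 30% power in the half-diluted case. It supports reporting an estimate with its interval rather than relying on a test.

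**Conclusion.** The concern holds in limited form. The article selects gender and age for supporting analyses and states no analysis of clinical effect by time from onset, although its rationale rests on timing and entry runs to day 12. The primary test remains valid, and neither the eligibility rule nor the virological outcomes are at fault.

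The possible loss of power, to 52%, 43% or 26%, is illustrative. It depends on an assumed late share, an assumed late HR of 1.0, and on reading 1.4 as the effect in early patients, whereas the sample size section states it for the trial as a whole. The omission does not cause that loss. It leaves the stated plan without a means of examining it. If the SAP already contains an onset-time analysis, only the article's list needs to be brought into line.

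**What to change.** 1. **Section 3.18.3.** Add a treatment-by-days-from-onset analysis for TTCI (Cox) and mortality (logistic). Use days from onset as a continuous variable, with one cut-point fixed before unblinding. Report the interaction estimate with its confidence interval, label it exploratory, and interpret it alongside the two virological outcomes.
2. **Items 20a and 21b.** Include days from onset to randomization as a baseline covariate in the Cox model, the same at both looks and fixed before the interim analysis. It is not a stratification factor, and it has to be established anyway to apply the entry criterion.

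**Cost.** Analysis wording only: no new patients, visits or samples, provided the number of days is recorded and not merely that the criterion was met. The drawback is one more exploratory analysis with low power, which will often be inconclusive and restores none of the overall power lost if the effect is diluted.
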